### Data processing

PROM data collection is paper based, with participant number 55 onwards being offered the option of completing PROMs online. Once paper-based 12-week, 24-week and 52-week PROMs are completed the participant seals them in a windowless opaque envelop and returns them to the researchers (postage pre-paid). These are securely stored and subsequently opened in batches by an individual blinded to group allocation, who inputs the data into a holding database for subsequent transfer into SPSS for reporting and statistical analysis. For audit purpose, after inputting each batch, a ‘read-only’ copy is stored in a separate protected folder. A separate copy is used for data screening and cleaning, guided by good practice [33] and may include self-evident corrections [34] where appropriate. While filters and error alerts will reduce inputting errors, 20% of entries will be cross-checked against the paper PROMs for discrepancies. Data changes will be recorded for blinded adjudication. For audit purposes a copy of the cleaned and checked data will also be saved as a ‘read-only’ copy and stored separately. The design of the e-PROMs does not permit questions to be left unanswered, mitigating against problems of incomplete data and once the participant completes their PROM the original dataset is locked against further alterations. The system permits data transfer into SPSS.

The research team and statistician will conduct the analysis. The statistician will conduct the primary outcome analysis independently and is blinded to group allocation. Data and reason for any patient excluded prior to randomisation will be reported, but not carried into the main analysis. Descriptive statistics will be produced, within and between each intervention group(s) for demographics and outcomes at all data time points. Continuous data will be summarised as mean and standard deviation and confidence intervals (CI) (95% CI and *p* value threshold ≤ 0.05) for the PROM outcome data. Median and interquartile ranges will be used where appropriate statistical assumptions are not met, whereas categorical data will be presented as frequencies and proportions and analysed using either chi-square or Fisher’s exact test as indicated (*p* value of ≤ 0.05). Non-parametric tests will be employed where appropriate. Analysis will be conducted on the intention-to-treat (ITT) basis.

To test the primary outcome measure hypothesis that the EMADE physiotherapy intervention, as described will perform better than usual care, the difference in group means of the primary outcome, OMAS values at 12 weeks post surgery, will be statistically compared. This will be through applying an independent *t* test with significance taken as *p* value of ≤ 0.05 and the inclusion of confidence intervals (CI at 95% CI and *p* value of ≤ 0.05 threshold). Where data is not found to be normally distributed such that parametric tests cannot be utilised, the non-parametric Mann-Whitney *U* test will be employed (*p* value ≤ 0.05).

There is a lack of consensus in the academic literature on how to handle missing data [35, 36]. However, based on the 120 sample size, the following sequential approach will be applied for the primary outcome:If missing data is 5% or less, conduct analysis based on complete-case analysisIf missing data is greater than 5% and up to 10%:Conduct analysis based on pairwise deletion (assuming missing at random (MAR)) and thenConduct multiple imputation analysisIf these two analyses yield comparable results, then it will be assumed that the missing data has not influenced the outcome of the trialIf the two analyses yield notable differences, to accommodate for the missing data, sensitivity analysis will be conducted based on the statistician’s adviceIf missing data exceeds 10%, detailed discussions will be held with the study statistician

Interpretation of secondary outcome and sub-group analysis will require caution due to risks of type II errors and, because of where post hoc analysis may demonstrate association, causation may not be supported. Secondary analyses will be performed for hypothesis generation. The difference in group mean scores for the secondary outcomes; EQ-5D-5 L and A-FORM at 12 weeks post surgery will be analysed in a similar manner to the primary outcome. The one-way analysis of covariance (ANCOVA), including follow-up time as a covariance, will be applied to assess these outcomes across the complete study period.

Adjustment for baseline scores, through analysis of covariance, will be conducted for OMAS, EQ-5D-5 L and A-FORM and compared with unadjusted scores. Impact of covariates will be further explored through regression analysis. Initial analysis for co-variates where significance is nearly reached (*p* > 0.10) will be taken forward into a statistical model. Due to the bimodal impact of age and sex, these will be included in this analysis. Other exploratory analysis for potential covariates may include impact of smoking, previous level of physical activity, type of fracture (AO classification), complexity of surgical repair and any subsequent removal of metal work; most notably removal of syndesmosis screw(s) for which stratification was applied at randomisation. Analysis will also be conducted using modified ITT by excluding those participants who attend only one session or less of EMADE sessions.

Sub-groups will include return to work for those unable to work due to their ankle fracture at the time of randomisation, and similarly, return to driving for those unable to drive due to their ankle fracture at the time of randomisation. Frequency of complications will be described but, based on the published literature, it is anticipated that frequency will be sufficiently low not to warrant statistical analysis.

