### Allocation and Blinding

An online computer service, www.sealedenvelope.com is used for randomisation. This facility generated the codes concealed from the research team, on a 1:1 allocation basis to either group, with random order of permuted blocks (sizes of 4, 6 and 8). Over the duration of the trial, there is greater potential that those with syndesmosis screw(s) may require further surgery. To mitigate against risk of allocation imbalance, stratification of this sub-group will be designed into the randomisation.

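### The primary t test leaves out the randomisation stratum and baseline OMAS, and a normality finding can replace it with a test that does not estimate the 10-point mean difference

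*Protocol article*

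**What the plan says.** All references are to the protocol article.

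- **Primary effect measure (Data processing):** "the difference in group means of the primary outcome, OMAS values at 12 weeks post surgery, will be statistically compared".
- **Primary test (same section):** "This will be through applying an independent *t* test with significance taken as" p ≤ 0.05. No covariate is named.
- **Fallback (same section):** "Where data is not found to be normally distributed such that parametric tests cannot be utilised, the non-parametric Mann-Whitney *U* test will be employed".
- **Randomisation (Allocation and Blinding):** for patients with syndesmosis screws, "To mitigate against risk of allocation imbalance, stratification of this sub-group will be designed into the randomisation".
- **Baseline:** OMAS is collected at 2 weeks (Secondary outcome measures), and randomisation follows only once baseline measures are recorded (Participant timeline).
- **Adjusted analysis (Data processing):** "Adjustment for baseline scores, through analysis of covariance, will be conducted for OMAS" and two other scores, to be set beside the unadjusted results. Syndesmosis appears only among optional exploratory covariates, and there as later screw removal, which happens after randomisation.
- **Sample size (Sample size calculations):** 120 evaluable patients for a 10-point OMAS difference, SD 19.5, 5% significance, 80% power.

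**The concern.** Two pieces of pre-randomisation information are available for every randomised patient, and the primary test uses neither. When randomisation is balanced within a stratum that predicts outcome, the true variance of the difference in means is smaller than the one an unadjusted t test estimates. The standard error is then too large, and part of the benefit of stratifying is lost. Leaving out a predictive baseline score also gives away precision.

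The fallback raises a different problem. The hypothesis and the sample size are stated as a difference in means on the OMAS scale. If the test is swapped after the distribution has been inspected, the primary p value no longer refers to that quantity and comes with no estimate or interval in OMAS points. OMAS is bounded at 0 and 100 and built from nine Likert-type items, so some departure from normality is likely.

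**Working it through.** **1. Reproduce the stated sample size.** Inputs from Sample size calculations: difference 10, SD 19.5, two-sided 5% (sidedness is not stated, but one-sided gives 96), power 80%.

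n per arm = 2 × (1.960 + 0.842)² × 19.5² / 10² = 59.7, so 60 per arm and 120 in total. The figure reproduces. Power at 60 per arm is 80.2% by the normal approximation and 79.6% by the noncentral t. The calculation is for an unadjusted difference in means, so the planned t test matches it.

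**2. Effect of covariate adjustment.** Residual SD = 19.5 × √(1 − r²), where r is the correlation of the covariates with 12-week OMAS. The documents give no r, so a range is assumed. Power is noncentral t at 60 per arm and is the same to one decimal whether one or two covariates are charged.

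| r (assumed) | Residual SD | Power | 95% CI half-width (points) |
|---|---|---|---|
| 0 (plain t test) | 19.50 | 79.6% | 7.05 |
| 0.1 | 19.40 | 80.0% | 7.02 |
| 0.2 | 19.11 | 81.1% | 6.91 |
| 0.3 | 18.60 | 83.2% | 6.73 |
| 0.4 | 17.87 | 86.0% | 6.46 |

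The low end is plausible. At 2 weeks patients are non-weight-bearing and are advised to choose the poorer answer when unsure (Secondary outcome measures), so baseline OMAS may sit near its floor.

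**3. Effect of ignoring the stratum.** Let p be the share with screws and D their difference in mean OMAS (both assumed). With balance within strata, the true SD behind the comparison is s = √(19.5² − p(1 − p)D²), while the t test uses 19.5. True two-sided type I error = 2 × [1 − Φ(1.960 × 19.5 / s)].

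- p = 15%, D = 5: s = 19.42, true level 4.9%.
- p = 25%, D = 10: s = 19.01, true level 4.4%.
- p = 35%, D = 15: s = 18.14, true level 3.5%.

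The error is on the conservative side throughout.

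**4. The switch to Mann-Whitney.** The protocol article names no normality test, so Shapiro-Wilk p < 0.05 in at least one arm is assumed as the trigger. Simulated scores were bounded 0–100 in 5-point steps (assumed), with SD 19.5 before rounding and clipping, 55 or 60 per arm and means 50 to 75, in two shapes.

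| Mean (55 per arm) | Switch rate, rounded beta | Switch rate, rounded and clipped normal |
|---|---|---|
| 50 | 28% | 13% |
| 60 | 53% | 17% |
| 65 | 82% | 27% |
| 70 | 98% | 60% |
| 75 | 100% | 93% |

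Across all these settings the t test's type I error stayed between 4.4% and 5.6% (4,000 replicates each), so the switch is not needed to protect the error rate. Its frequency runs from about 13% to 100%, depending on a distribution that is not known in advance.

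**The case against.** The strongest reply is that nothing here is wrong. The t test is valid, it is the test the 120 patients were calculated for, and ignoring a prognostic stratum cannot inflate false positives. Baseline ANCOVA is already planned, one test is clearly designated for the primary hypothesis, and the statistician is blinded to allocation. All of that stands, and it limits the point to efficiency and to what is estimated.

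Four stronger readings are tempting, and the documents do not support them.

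- **That the choice of test leaves the trial underpowered.** With 156 randomised and 30% lost, 156 × 0.7 = 109 remain, and unadjusted power is 75.7%. That shortfall comes from inflating 120 by 1.3 instead of dividing by 0.7, which is a separate matter.
- **That the stratum is known to predict 12-week OMAS.** The stated reason for stratifying is possible further surgery over the course of the trial. The standard-error argument is therefore conditional.
- **That Mann-Whitney costs power.** Under normality it costs about 2 points (78.4% against 80.2%). In simulated skewed scores with control means 65 and 75 it had more power (85% and 96%, against about 79% for the t test). The objection is to the lost mean difference.
- **That a switch is nearly certain.** The condition, "Where data is not found to be normally distributed such that parametric tests cannot be utilised", can be read as stricter than a failed normality test, and the exact criterion may properly sit in a statistical analysis plan. What stands is that the article itself permits the swap.

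**Conclusion.** The point holds as a recommended improvement and does not invalidate the analysis. The primary test omits the stratum as randomised and the baseline OMAS. The gain from including them, at 60 per arm, runs from about 0.4 points of power at r = 0.1 to 6.4 points at r = 0.4. It rests on an assumed correlation, and a floor effect at 2 weeks could keep it small. If the stratum is prognostic, the t test runs at about 3.5% to 4.9% instead of 5%, for an assumed share of 15–35% and effect of 5–15 points.

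The firmer part does not depend on r. The article allows a data-dependent change to a test that does not estimate the 10-point mean difference behind the sample size, and at 55 to 60 per arm that change is not needed for error control. How often it would happen cannot be fixed from the documents.

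**What to change.** Make the primary analysis an ANCOVA of 12-week OMAS on arm, baseline OMAS and syndesmosis stratum as randomised. Later screw removal should not stand in for the stratum, because it follows randomisation. Report the adjusted mean difference with its 95% CI, using robust standard errors, whatever the distribution looks like. Keep the unadjusted t test and the Mann-Whitney test as named sensitivity analyses, and delete the clause that lets one replace the other as primary.

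No new data are needed. The cost is two degrees of freedom and a wording change, to be made before unblinding.

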## Sample size, data processing and statistical methods

### Sample size calculations

It was estimated that a total of 120 participants will be required based on a minimal clinical important difference of 10 points on the OMAS, with a standard deviation of 19.5, significance level of 5% and powered at 80%. Allowance for attrition was set initially at 20% but, due to higher-than-expected dropout rates, this was increased to 30%, yielding a target of 156 to enter the study at randomisation.

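### The missing-data rule for the 12-week OMAS names a method only up to 10% missing although the sample size builds in a 23% loss, and it wrongly reads agreement of two analyses as proof of no influence

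*Protocol article*

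**What the plan says.** The rule stands in the protocol article under Data processing, after the primary t test: "based on the 120 sample size, the following sequential approach will be applied for the primary outcome". It has three branches.

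- **5% or less missing:** complete cases.
- **Above 5% and up to 10%:** "Conduct analysis based on pairwise deletion (assuming missing at random (MAR"), followed by multiple imputation. If the two results are comparable, the missing data are taken not to have affected the trial's result. If they differ notably, a sensitivity analysis follows on the statistician's advice.
- **Above 10%:** if "missing data exceeds 10%, detailed discussions will be held with the study statistician". Nothing further is fixed.

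The primary test is an unadjusted independent t test on the 12-week score. The same section commits to intention to treat and says that the statistician runs the primary analysis independently, blinded to allocation.

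Under Sample size calculations, "It was estimated that a total of 120 participants will be required". The section continues: "Allowance for attrition was set initially at 20% but, due to higher-than-expected dropout rates", it was raised to 30%, giving 156 at randomisation.

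**The concern.** The sample size section and the missing-data rule do not fit together. One plans for a substantial loss because loss had already been seen; the other gives methods only for a small loss. What the protocol fixes in detail is the unlikely case.

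Two further defects lie inside the rule. The phrase about the 120 sample size can be read as making 120 the denominator, which would hide every loss down to that number. And the 5–10% branch draws a conclusion, no influence, that its comparison cannot support.

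At stake is the primary estimate. Participants and therapists are unblinded, the outcome is self-reported and may be returned by post or online, and only the EMADE arm has weekly visits during the intervention. It is plausible that those who do not return the 12-week form differ in outcome, and differ by arm.

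**Working it through.** **Inputs.** Difference 10 points, SD 19.5, 5% significance, 80% power, 120 evaluable, allowance 20% then 30%, target 156 (Sample size calculations); 1:1 allocation (Trial design and study setting); cut-offs of 5% and 10% (Data processing).

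**1. The plan's own figures.** Per arm, n = 2 × (1.96 + 0.8416)² × (19.5/10)² = 2 × 7.849 × 3.8025 = 59.7, so 60 per arm and 120 in total. This reproduces the stated figure with a two-sided test. The target is 120 × 1.30 = 156; dividing instead, 120/0.70, would give 172. The loss built in is therefore 156 − 120 = 36, and 36/156 = 23.1%.

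**2. Which branch applies.** Ten per cent of 156 is 15.6, so at most 15 may be missing before the methods run out. The built-in loss of 36 is more than twice that. If each participant is missing independently, the chance of 15 or fewer missing is about 0.0004 at a 20% rate and 0.00001 at 23.1%. The allowance is not tied to 12 weeks, and no 12-week rate is given. For a named method to apply on this base, 12-week loss would have to be no more than 15/36 = 42% of the built-in loss.

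**3. The denominator.** Take 156 randomised and 120 returned.

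| Base | Missing | Branch |
|---|---|---|
| All randomised (156) | 36/156 = 23.1% | discussion only |
| Shortfall from 120 | 0/120 = 0% | complete cases |

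On the second base, 108 returns would read as 12/120 = 10% missing, while 48/156 = 30.8% of those randomised had no outcome.

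**4. Pairwise deletion.** With one outcome and no covariate, dropping incomplete pairs and dropping incomplete cases give the same data set, so the first step above 5% repeats the step below it. Each arm mean is then unbiased only if missingness is unrelated to the outcome within that arm. The difference otherwise escapes bias only if the two arms' errors cancel. Missing at random also allows loss to depend on observed scores that predict the outcome, such as the 6-week OMAS; the unadjusted t test does not handle that. The label attached is therefore too weak for the method.

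**5. Agreement as evidence.** If loss depends on the unseen score, deletion and missing-at-random imputation are both biased, and can be so by similar amounts. An illustrative simulation assumed no true effect, SD 19.5, 78 per arm, correlation 0.3 between baseline and outcome, about 8% missing, and low scorers lost selectively in one arm only. Imputation was a within-arm regression on baseline (point estimates only). Complete-case bias was +1.3 points and imputation bias +1.2; the two estimates differed by about 0.2 points on average. The rule would have declared no influence. This is a strong mechanism: 1.3/0.078 implies a gap of about 17 points, so it shows that agreement is uninformative, not how large the bias will be.

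**6. Size.** Within an arm, seen mean − full mean = f × (seen − unseen), with f the missing fraction. With equal f, the bias in the treatment difference is f × D, where D is the between-arm difference in that gap. The documents give no D; 5 to 10 points is assumed.

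| f | D = 5 | D = 10 |
|---|---|---|
| 10% | 0.5 | 1.0 |
| 23.1% | 1.2 | 2.3 |

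**The case against.** Several points on the other side have weight.

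- **A method above 10% may be left to the analysis plan, which is not shown.** On its own, a silent protocol would be no finding. Here, however, the protocol fixes the rule, sets its cut-offs and states an inference from it.
- **The statistician is blinded.** This stands as real mitigation. A reader might infer that the method will be picked knowing results by arm; the documents do not say so. Blinding still does not prespecify a method.
- **The nominal 30%.** A reader might take it that 30% of 156, about 47, are expected missing. The target is 120 × 1.30, so the loss actually built in is 23.1%. The allowance may also reflect loss up to 52 weeks, although it was applied to the sample size for the 12-week outcome.
- **The 120 base.** A reader might state as fact that losses are counted against 120. The phrase may mean only that the cut-offs were chosen for a trial of that size, and the intention-to-treat commitment points to all randomised. What stands is the ambiguity.
- **Missing completely at random.** A reader might say complete cases need this. They do not: loss that differs only by arm causes no bias.
- **The no-influence inference operates only between 5% and 10%.** Correct. If loss exceeds 10% of those randomised, it does not come into play, and within its range the illustrative bias is at most 0.5–1.0 points.
- **Baseline-adjusted covariance analysis is planned.** It allows loss to depend on baseline, but it is a comparison with the unadjusted result, not the missing-data method, and it does not address loss that depends on the unseen score.

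**Conclusion.** The point holds in this form. The rule specifies an analysis only up to 10% missing, while the sample size builds in 23.1%, so the branch most likely to apply consists of discussion with a blinded statistician. The denominator is unclear, and one natural reading would turn a 23.1% loss into 0% and select complete cases, against the intention-to-treat commitment. The 5–10% branch uses complete cases under another name, gives them an assumption that is too weak, and draws a conclusion that the comparison cannot deliver; what counts as comparable or notable is not defined either.

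The illustrative bias is 12–23% of the 10-point minimal important difference at the built-in loss, and 5–10% of it at the 10% cut-off. Both rest on the assumed 5–10 point gap and on equal loss in the arms. The documents do not show that bias will occur or in which direction; they show that the rule would neither prevent nor reveal it.

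**What to change.** Before the primary analysis, amend the protocol and the analysis plan as follows.

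1. Define missing as no 12-week OMAS among all participants randomised.
2. Replace the stepped rule with one prespecified missing-at-random analysis, used at any level of missingness: multiple imputation by arm, or an equivalent likelihood model, with baseline and 6-week OMAS, the syndesmosis stratum, age and sex. The choice between the two is a matter of preference. The early scores may predict only modestly, since unsure participants are told to choose the poorer answer while non-weight-bearing.
3. Always add a delta-adjusted sensitivity analysis for data missing not at random, with delta varied separately by arm.
4. Report complete cases as supportive.
5. Delete the sentence that infers no influence from agreement.

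The cost is wording and a modest amount of extra analysis. No new data are needed: the OMAS at 2 and 6 weeks and the stratum are already collected, and age and sex are already planned as covariates.

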#### Secondary objectives include

A key secondary objective is to determine whether, in this patient group, EMADE will perform better than usual care in the short term (12 weeks post surgery) as measured by the EQ-5D-5 L quality of life measure and the Ankle-Fracture Outcome of Rehabilitation Measure (A-FORM)To determine whether, in this patient group, EMADE will perform better than usual care, in the medium- and long-term (24 and 52 weeks post surgery, respectively), as measured by the OMAS, EQ-5D-5 L and A-FORMTo explore the cost-effectiveness of EMADE

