#### Secondary outcome measures

Secondary outcomes including the OMAS collected at 2 and 6 weeks post surgery, as baseline and end-of-intervention measures, respectively and at 24 and 52 weeks post surgery, as medium- and long-term follow-ups. Other secondary outcomes include: the Ankle-Fracture Outcome of Rehabilitation Measure (A-FORM) [29] and the EQ-5D-5 L [30] PROMs, which are collected at the same time points as the OMAS. Other function-focussed outcomes include the Physical Activity Record Scale (PARS) [31], the Clinical Physical Activity Questionnaire (CPAQ) [32], the use of walking aids, return to work and return to driving. X-ray findings and adverse events are also recorded.

When answering Likert-styled questions within the PROMs, if a participant is unsure which Likert option to select, they are advised to select the poorer outcome. This approach is particularly pertinent at the 2-week and 6-week time points, when answering function-related questions such as walking, as post-operative clinical instructions would have been to remain non-weight-bearing. This is not an anticipated concern for the primary outcome, being at 12 weeks, nor the subsequent follow-ups.

Objective measures are included at the 2-week and 6-week time points: non-weight-bearing dorsiflexion and plantar flexion ROM and, ankle (figure-of-8) and calf (circumference) measures. Participants will be invited to attend for repeated outcome assessments at 12 weeks, 24 weeks and 52 weeks, with the additions of weight-bearing dorsiflexion, walking speed, balance and isokinetic plantar-flexion strength. Those declining will be encouraged to complete and return the appropriate PROMs questionnaires.

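### The one-way ANCOVA with follow-up time as a covariate treats repeated EQ-5D-5L and A-FORM scores as independent and averages the arm effect over visits, so it does not serve the 24- and 52-week objectives

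*Protocol article*

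**What the plan says.** All statements are in the Protocol article.

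- **Objectives.** Under the secondary objectives, EMADE is to be compared with usual care "in the medium- and long-term (24 and 52 weeks post surgery, respectively), as measured by the OMAS", and by EQ-5D-5L and A-FORM as well. Weeks 24 and 52 are thus two separate questions on three instruments.
- **Data.** OMAS is scored at 2 weeks (baseline) and at 6, 12, 24 and 52 weeks. The section on secondary outcome measures describes A-FORM and EQ-5D-5L as "PROMs, which are collected at the same time points as the OMAS". One person can therefore contribute four scores after randomisation.
- **Analysis at 12 weeks.** "The difference in group mean scores for the secondary outcomes; EQ-5D-5 L and A-FORM at 12 weeks post surgery will be analysed in a similar" way: an independent t test, as for the 12-week OMAS.
- **Analysis over time.** The next sentence reads: "The one-way analysis of covariance (ANCOVA), including follow-up time as a covariance, will be applied to assess these outcomes across the complete study period". The outcomes it points back to are EQ-5D-5L and A-FORM.
- **Other analyses that could reach later visits.** "Descriptive statistics will be produced, within and between each intervention group(s) for demographics and outcomes at all data time points". Also: "Adjustment for baseline scores, through analysis of covariance, will be conducted for OMAS, EQ-5D-5 L and A-FORM and compared with unadjusted scores". The latter names no visit.
- **Status.** "Secondary analyses will be performed for hypothesis generation".

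The statistical sections mention no participant effect, repeated-measures structure, robust standard error or arm-by-time term.

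**The concern.** For follow-up time to act as a covariate over the whole study, the data set must hold one row per score. Two problems follow.

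First, scores from one person are normally positively correlated, and arm is a between-person factor. An analysis with independent errors counts four scores as four people's worth of information about the arm difference. Its standard error is too small, its confidence interval too narrow, and it rejects a true null too often.

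Second, with arm as the only factor and time as a covariate, the model fits one straight-line time trend and one constant arm difference. A benefit that is present early and gone by a year would be reported as a single intermediate value. For an intervention that ends at 6 weeks, that pattern is plausible and is what the separate 24- and 52-week objectives are meant to detect.

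The scope of the sentence is a smaller point. As worded it covers EQ-5D-5L and A-FORM but not OMAS, which the same objective names.

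**Working it through.** **1. The plan's own figure.** The sample size rests on a "minimal clinical important difference of 10 points on the OMAS, with a standard deviation of 19.5", 5% significance and 80% power. Two-sided:

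n per arm = 2 × (1.960 + 0.842)² × 19.5² / 10² = 59.7, so 60 per arm and 120 in total.

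This reproduces the stated 120. It concerns one score per person at 12 weeks and is not in dispute. It supplies the 60 per arm used below.

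**2. Inputs for the check.** From the document: four follow-up visits (6, 12, 24, 52 weeks), 60 per arm, SD 19.5. Assumed, because the document gives no value: equal within-person correlation ρ of 0.3, 0.5 or 0.7 between any two visits, and complete data.

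**3. No baseline adjustment, time trend fitted correctly.** With m scores per person, the true variance of the arm difference is about 1 + (m − 1)ρ times what the model reports. The actual type I error is 2 × [1 − Φ(1.96 / √(1 + (m − 1)ρ))]. For m = 4:

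| ρ | variance ratio | SE too small by a factor of | type I error (formula) | simulated, 60 per arm |
|---|---|---|---|---|
| 0.3 | 1 + 3(0.3) = 1.9 | 1.38 | 15.5% | 15% |
| 0.5 | 1 + 3(0.5) = 2.5 | 1.58 | 21.5% | 22% |
| 0.7 | 1 + 3(0.7) = 3.1 | 1.76 | 26.6% | 26% |

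At ρ = 0 the simulation returns about 5%, as it should. If only the 12-, 24- and 52-week scores enter (m = 3), the formula gives 12%, 17% and 21%.

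**4. With the baseline score as a covariate.** Under equal correlation, conditioning on baseline lowers the correlation among follow-up scores to ρ/(1 + ρ), that is 0.231, 0.333 and 0.412. The variance ratios for m = 4 become 1.69, 2.00 and 2.24, and the type I error 13%, 17% and 19%. Simulation gives 13%, 17% and 19%.

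**5. With a curved recovery.** If recovery is fast and then flattens, a straight line in time fits badly. The misfit goes into the residual variance, enlarges the model's standard error and partly offsets the understatement. With assumed means of 25, 55, 70 and 80 at 6, 12, 24 and 52 weeks and SD 19.5, simulation gives about 10%, 15% and 20% without baseline adjustment, and about 8%, 10% and 9% with it. The OMAS SD stands in for the other two instruments here, since no SD is given for them.

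**6. What the model estimates.** Suppose that the true differences are 10, 5 and 0 points at 12, 24 and 52 weeks. The single arm coefficient estimates their mean, (10 + 5 + 0)/3 = 5.0; simulation returns 4.98. Nothing in that output shows that the 52-week difference is zero.

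**The case against.** The other side has four good arguments.

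- **Status.** The article calls the secondary analyses hypothesis-generating and asks for caution. The 12-week OMAS, EQ-5D-5L and A-FORM comparisons use one score per person and are untouched. This stands and lowers the severity. The caution itself, though, names type II errors, whereas this model errs towards type I.
- **Other routes to 24 and 52 weeks.** A reader might infer that the plan yields nothing at those visits. The document does not support that: between-group summaries are planned at all time points, confidence intervals are promised for the patient-reported outcomes, and the baseline-adjusted ANCOVA covers all three instruments without being limited to 12 weeks. What remains is that neither is assigned to weeks 24 and 52 as the test of the objective.
- **Consistency of the harm.** A reader might also infer that the medium- and long-term objectives would be decided on inflated p-values. That does not follow. The pooled model gives no visit-specific p-value, and comparisons made visit by visit would not carry this inflation. The inflation belongs to the pooled whole-period test alone.
- **Magnitude.** The 15% to 27% range is the high-side case. Baseline adjustment and a curved recovery both reduce it, as steps 4 and 5 show. This stands; none of the cases with positive correlation examined came down to 5%.

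It may also be said that the sentence is loose wording for a repeated-measures model, or a matter for the analysis plan. An unstated method could be left to that plan. Here a specific method is named, and an analysis plan that followed it would inherit the fault.

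**Conclusion.** The point holds for the named whole-period model. Applied as written to repeated scores, it ignores within-person correlation. With four follow-ups and an assumed correlation of 0.3 to 0.7, the nominal 5% test has a type I error of about 15% to 27% unadjusted (about 10% to 20% under the assumed curved recovery) and about 8% to 20% with baseline adjustment. The size depends on the assumed correlation, the number of visits pooled and the recovery curve.

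The model also estimates an average over visits, so it does not answer the 24- and 52-week objectives, and its wording leaves out OMAS. No other test is expressly tied to those visits.

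The primary 12-week analysis and the sample size are not affected. Because the analyses concerned are secondary and exploratory, this is a defect that should be corrected, not one on which the trial's main conclusion turns.

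**What to change.** Replace the sentence with a linear mixed model for repeated measures, applied to OMAS, EQ-5D-5L and A-FORM alike. Include follow-up time as a category (6, 12, 24, 52 weeks), arm, arm-by-time, baseline score and syndesmosis stratum, with a stated within-person covariance. Report the arm difference and its 95% confidence interval at 12, 24 and 52 weeks.

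An acceptable alternative is the baseline-adjusted ANCOVA that the article already names, run separately at each of those three visits and for all three instruments. It uses one score per person per analysis, so the independence problem does not arise.

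Either way, state that the 12-week OMAS t test remains the primary analysis unless that is changed separately.

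The cost is wording in the protocol or the analysis plan. No extra data or participants are needed, and SPSS, the package that the article names, fits mixed models.
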